# EMBalance - validation of a decision support system in the early diagnostic evaluation and management plan formulation of balance disorders in primary care: study protocol of a feasibility randomised controlled trial

**DOI:** 10.1186/s13063-016-1568-x

**Published:** 2016-09-05

**Keywords:** Vestibular disease, Dizziness, Vertigo, Decision support system, Randomised controlled trial, Feasibility study

## Abstract

**Background:**

Balance problems are caused by multiple factors and often lead to falls and related fractures, bringing large socio-economic costs. The complexity of balance control mechanisms, the lack of medical expertise, and the absence of specialised equipment contribute to the delayed or incorrect diagnosis and management ofthese patients. Advances in computer science have allowed the development of computer systems that support clinical diagnosis and treatment decisions based on individualised patient data. The aim of the EMBalance decision support system (DSS) is to support doctors facing this clinical challenge, to make a definitive diagnosis and implement an effective management plan. The EMBalance study will determine the accuracy of this supportive tool when used by non-specialist doctors. This study is funded by the European Union’s Seventh Framework Programme.

**Methods/design:**

EMBalance is a proof-of-concept study designed as a non-commercial, international, multi-centre, single-blind, parallel-group randomised controlled trial to be carried out at four clinical sites in the United Kingdom, Germany, Greece and Belgium. The study is comprised of three stages: internal pilot, phase I (diagnosis) and stage II (management). For this purpose, 200 patients presenting with persistent dizziness (>3 months’ duration) to primary care services will be randomised to either the intervention group (diagnostic assessment with the DSS) or a control group (diagnostic assessment without the DSS). Patients allocated to the intervention group will be assessed by a doctor with the support of the EMBalance DSS, while patients allocated to the control group will receive a visit as per standard practice. Ultimately, all patients’ diagnoses and management plans will be certified by a consultant in neuro-otology.

**Discussion:**

EMBalance is the first trial to test the accuracy of a DSS in both the diagnosis of and the management plan for vestibular disorders across the healthcare systems of four different countries. The EMBalance study is the result of a combined effort of engineers and physicians to develop an accurate tool to support non-specialist doctors, with no risk for the patient. This trial will provide reliable information about the benefits of implementing DSSs in primary care while supporting the feasibility of testing the EMBalance algorithms in further research.

**Trial registration:**

ClinicalTrials.gov NCT02704819. Registered 29 February 2016.

**Electronic supplementary material:**

The online version of this article (doi:10.1186/s13063-016-1568-x) contains supplementary material, which is available to authorized users.

## Background

Human balance is crucial for an individual’s mobility and independence. Balance depends on integration of vestibular, vision and proprioceptive sensory input within the central nervous system and generation of appropriate motor and other responses that support stance, locomotion and orientation [1]. Dizziness and imbalance symptoms are amongst the most common reasons for visits to a doctor and affect up to 30–40 % of the population by 60 years of age [2, 3]. Healthcare service provision to address vestibular disorders remains inadequate and is regarded as a low priority [4]. Non-specialist physicians may feel overwhelmed when faced with a patient complaining of ‘dizziness’, owing to the vagueness of this symptom and the plethora of underlying pathologies. Narrowing the symptom to the causative system (e.g., cardiovascular, neurological, otological) or as being iatrogenic (e.g., a drug-related adverse reaction) is a challenging process. Unsurprisingly, in both the United States and the United Kingdom, patients require an average of 4.5 visits with their healthcare providers before receiving a correct diagnosis and appropriate treatment plan [4].

The complexity of balance control mechanisms, the lack of medical expertise, and the absence of specialised equipment can be contributory factors to this late diagnosis and the resulting mismanagement of patients with balance disorders [5, 6]. This has a considerable socio-economic impact on the affected individual and the individual’s family and exerts a high burden on society and the health services [7]. Misdiagnosis and mismanagement lead to increased personal burden on the patient and a wide-scale burden on health economics and society [8].

Advances in computer science and artificial intelligence have allowed the development of computer systems that support clinical diagnosis or therapeutic and treatment decisions based on individualised patient data [9, 10]. Decision support systems (DSSs) in particular are aimed at codifying and strategically managing biomedical knowledge to handle clinical challenges using mathematical modelling tools, medical data-processing techniques, and artificial intelligence methods [11–13]. However, a review of existing DSSs used in medicine demonstrated that there are but few successful integrated software systems or stand-alone tools which address the early diagnosis and effective management of balance disorders [14]. Current DSSs mainly target diagnosis, but none provide management and/or rehabilitation support. There is also limited information in the time domain (follow-up visits) and very limited literature on detailed balance-related models, while there are no vestibular models currently integrated into a DSS or used in clinical practice, and no patient-specific models [14].

EMBalance is a European project funded by the European Union’s Seventh Framework Programme for Research. Its aim is to develop a DSS to support clinical decision-making, facilitate accurate diagnosis and advise on efficient treatment of balance disorders. The final outcome of the EMBalance project will be an Internet-based platform provided to primary and secondary care physicians across specialties, all levels of training, and with no geographical boundaries, with the objectives of early diagnostic evaluation and effective management of balance disorders.

### The EMBalance decision support system

The EMBalance DSS is a multilanguage platform that consists of three modules: the database, the back end and the graphical user interface (GUI):The database of the system is the implementation of the repository. The repository has been modelled using entity relationship modelling notation and MySQL Workbench, an open source software programme that has been developed by Oracle (Redwood Shores, CA, USA) and supports a relational database-modelling and development approach. MySQL Workbench was also used for the administration of the repository. In total, the EMBalance repository is composed of 48 entities, including instance tables (actual clinical data collected from 1100 patients’ records), and type tables, which are the values used to populate an attribute of the instance tables (e.g., patient occupation). Of these, 16 tables store many-to-many relationships.The back end is used to implement the functionalities of the system and is composed of the configuration, the entities, the services and the repository.The GUI, also known as *front end*, is a user-friendly and easy-to-understand Internet-based tool that the clinician uses to input patient information, which subsequently feeds into the repository to generate assisted diagnosis and management outcomes. The interface has been developed using the Spring Framework for the back end of the tool and the Ext JS Framework for the GUI.

The primary users of the platform are non-specialist doctors (e.g., general practitioners), and its intended use has the following characteristics:The doctors can pace the process any way they see fit (e.g., by switching from history-taking to examination, stopping at any point or going back to medical history) or by stopping the process entirely.The doctors who use the DSS will be asked to exercise their clinical judgement in order to come up with a diagnosis or management plan.Although the EMBalance DSS platform will propose two or three diagnoses (with probability estimation for each), the doctors will be asked to either choose one of these or discard them and choose their own.At the end of this process, a specialist consultant will evaluate the patient to provide the definitive patient diagnosis and management plan; hence, patient care will not be affected other than by a longer-winded process for the patient.

## Methods/design

EMBalance is a feasibility and/or proof-of-concept study. It is designed as a non-commercial, international, multi-centre, single-blind, parallel-group randomised controlled trial (RCT) in accordance with the Standard Protocol Items: Recommendations for Interventional Trials (SPIRIT) guidelines [15] (see Additional file 1). The EMBalance study will be carried out simultaneously in the United Kingdom, Germany, Greece and Belgium. Both primary and tertiary care settings will be involved in these four countries. Table 1 provides the names of all participating clinical centres.

**Table 1 Tab1:** Participating centres: a comprehensive list of primary and tertiary care settings in the EMBalance study across Europe

Institution	Primary care setting	Tertiary care setting
Greece (University of Athens)	Hippocrateio Hospital	Hippocrateio Hospital
Belgium (Antwerp University)	Antwerp University Hospital	Antwerp University Hospital
Germany (University of Freiburg)	Freiburg University Medical Centre	Freiburg University Medical Centre
UK (University College London)	Keats Group Practice	National Hospital for Neurology and Neurosurgery
	Hampstead Group Practice	
	Parliament Hill Practice	
	James Wigg Practice	
	Brondesbury Medical Centre	

### Study participants and subject selection

The primary participants in this study are the non-specialist doctors as users of the DSS. This is to provide a proof of concept of the DSS in aiding diagnosis and management of the ‘dizzy’ patient. Participating doctors are divided into two groups: non-specialist doctors and overseeing experts.

#### Non-specialist doctors

The non-specialist doctors are defined as those who do not necessarily focus their clinical interest in balance disorders and who manage a range of patient categories. These doctors are the first point of access for patients seeking medical advice. All participating non-specialist doctors will be registered with their local medical boards, will have completed all required basic medical or other allied health education, and will have some clinical experience in managing patients in general. All non-specialist doctors will receive a 1-h training session during the site induction clinic on how to use the EMBalance DSS platform. The group of non-specialist doctors in each country will be composed of the following:UK: general practitionersBelgium and Greece: ear, nose and throat (ENT) residentsGermany: neurology residents

#### Overseeing experts

The overseeing experts will be members of the EMBalance consortium, who are highly experienced in the management of vestibular disorders. They will verify the appropriate diagnosis and management of each patient whilst being blinded to the previous use of the DSS by the non-specialist doctor. They will represent the gold standard for vestibular diagnosis and management. The expertise of the consortium is well documented, based on academic profile, years of experience, number of publications in relevant journals and conferences as well as relevant chapters in textbooks, and leading roles in educational and professional associations. The group of overseeing experts in each country is composed of the following:United Kingdom: consultants in audiovestibular medicine (AVM)Belgium and Greece: ENT specialists with >10 years’ expertise in AVM/neuro-otologyGermany: neurologists

Patients will be recruited into the study on the basis of the inclusion and exclusion criteria listed in Table 2.

**Table 2 Tab2:** Inclusion and exclusion criteria

Inclusion criteria
• Aged 18–90 years • Capable of understanding the information provided • Absence of dementia and/or uncontrolled psychiatric disorder • Vertigo or chronic dizziness exacerbated by head movements (<12 months) • Sub-acute presentation of dizziness (0–3 months) without presenting to emergency services
Exclusion criteria
• Aged <18 or >90 years • Learning disabilities or dementia • Uncontrolled psychiatric disorders • Pregnant and breastfeeding women • Incapable of or unwilling to give informed consent • Acute vestibular disorders (<3 months) presented at accident and emergency services

Patients who present with balance-related symptoms (specifically, vertigo or dizziness exacerbated by head movements) in primary care will be randomised into one of two groups:*Intervention group* (non-specialist doctor + DSS): Patients will be seen by a non-specialist doctor with the support of the DSS.*Control group* (non-specialist doctor − DSS): Patients will receive a standard visit with the non-specialist doctor without use of the DSS.

Ultimately, all patients’ cases will be reviewed by an overseeing expert, who will validate the clinical information collected. The overseeing expert will rate the diagnosis and management decisions made by the non-specialist doctor (both with and without the DSS) as correct or incorrect to assess whether the use of the EMBalance DSS leads to the correct diagnosis and improved management. In the event of disagreement, the overseeing expert will provide the final diagnosis and management plan for the patient according to evidence-based guidelines.

### Schedule of intervention

The EMBalance feasibility study is comprised of two parts: part I, in which patients are reviewed by the non-specialist doctors with or without the DSS to come to a diagnosis and devise a care plan, which is then reviewed by the overseeing expert; and part II, which refers to the management arm of the study and follow-up of all patients included. Part II will be carried out in the United Kingdom and Greece exclusively. A study diagram summarising the recruitment and intervention procedures is provided in Additional file 2.

#### Internal pilot

Owing to the limited time frame, this project includes an internal pilot phase. The first two non-specialist doctors and four to six patients entering the trial will provide a realistic overview of the potential barriers in connection with this protocol and study design. This is expected to happen during the first month of the trial. The pilot phase will follow the same study procedures described for parts I and II.

#### Part I: diagnosis and management plan assessment

On the day of recruitment, patients will initially be examined by the non-specialist doctor, either with or without the DSS, according to randomisation result. In both the + DSS and − DSS groups, each patient will undergo the investigations required, following which the non-specialist doctor will formulate an initial diagnosis and management plan. The patient will then be invited to attend a specialist neuro-otology clinic, where they will be seen by an overseeing expert to undergo a gold standard diagnostic process and to determine the management plan appropriate to the diagnosis, which will be compared with the management plan previously advised by the non-specialist doctor. The overseeing expert will review investigations carried out and results assessed by the non-specialist doctor. In the event that the doctor’s assessment differs from the conclusion of the expert, the latter will decide on the final diagnosis and management plan of the patient according to current evidence-based guidelines.

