### Trial objectives

#### Primary objectives

The primary objectives of this study are (1) to determine whether the EMBalance DSS is an accurate supportive tool for the diagnosis and management plan of dizziness and/or balance disorders when used by non-specialist doctors and (2) to establish the feasibility of testing the DSS in a large-scale RCT. These objectives will be measured as follows:Percentage of agreement between the diagnosis and management plan established by the non-specialist doctors (using the DSS and not using the DSS) and the gold standard as determined by an overseeing expert and according to current evidence-based guidelines for the diagnosis and/or management of these disorders

The primary outcome assessment criteria are shown in Table 3.

**Table 3 Tab3:** Primary outcome assessment criteria

Diagnosis (Dx)				
Single		Concurrent		
If doctorDx = expert Dx	100 %	If doctorDx_1_ + Dx_2_ = expertDx_1_ + Dx_2_		100 %
If doctorDx ≠ expert Dx	0 %	If doctorDx_1_ + Dx_2_ ≠ expertDx_1_ + Dx_2_		0 %
		If doctorDx_1_ = expertDx_1_ and doctorDx_2_ NA/≠ expertDx_2_		50 %
Management (Mng)				
Single		Multiple		
If doctorMng = expertMng	100 %	Maximum number of correct Mng plans = 2	If doctorMng_1,2_ = expertMng_1, 2_	100 %
If doctorMng ≠ expertMng	0 %		If doctorMng_1,2_ ≠ expertMng_1,2_	0 %
			If doctorMng_1_ = expertMng_1_ and doctorMng_2_ NA/≠ expertMng_2_	50 %
		Maximum number of correct Mng plans = 3	If doctorMng_1,2,3_ = expertMng_1,2,3_	100 %
			If doctorMng_1,2,3_ NA/≠ expertMng_1,2,3_	0 %
			If doctorMng_1_ = expertMng_1_ and doctorMng_2,3_ NA/≠ expertMng_2,3_	33.3 %
			If doctorMng_1,2_ = expertMng_1,2_ and doctorMng_3_ NA/≠ expertMng_3_	66.6 %
		Maximum number of correct Mng plans = 4	If doctorMng_1,2,3,4_ = expertMng_1,2,3,4_	100 %
			If doctorMng_1,2,3,4_ ≠ expertMng_1,2,3,4_	0 %
			If doctorMng_1_ = expertMng_1_ and doctorMng_2,3,4_ NA/≠ expertMng_2,3,4_	25 %
			If doctorMng_1,2_ = expertMng_1,2_ and doctorMng_3,4_ NA/≠ expertMng_3,4_	50 %
			If doctorMng_1,2,3_ = expertMng_1,2,3_ and doctorMng_4_ NA/≠ expertMng_4_	75 %
Diagnosis		100 % = correct		
		50 % = half correct		
		0 % = incorrect		
Management		100 % = fully correct		
		>50 % = majority correct		
		50 % = half correct		
		<50 % = partially correct		
		0 % = incorrect		

These criteria determine the level of agreement between the non-specialist doctor and the overseeing expert

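### The plan does not secure the independence of the expert reference standard from the non-specialist's conclusions that it is used to judge

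*Protocol article*

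**What the plan says.** Five parts of the protocol article bear on this.

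- **Gold standard.** Of the experts, the Overseeing experts section says: "They will represent the gold standard for vestibular diagnosis and management".
- **Review of diagnosis and plan.** The Schedule of intervention has the non-specialist see the patient "to come to a diagnosis and devise a care plan, which is then reviewed by the overseeing expert".
- **Review of tests.** Part I adds: "The overseeing expert will review investigations carried out and results assessed by the non-specialist doctor".
- **Rating.** The Overseeing experts section continues: "The overseeing expert will rate the diagnosis and management decisions made by the non-specialist doctor". The scale named there is correct or incorrect.
- **Primary outcome.** Under Primary objectives the measure is "Percentage of agreement between the diagnosis and management plan established by the non-specialist doctors" and the expert's gold standard, graded by Table 3.

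Two statements work in the plan's favour. The experts act "whilst being blinded to the previous use of the DSS by the non-specialist doctor", and the Blinding section lists them as blinded. In Part I patients attend a specialist clinic, where "they will be seen by an overseeing expert to undergo a gold standard diagnostic process".

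**The concern.** The primary outcome measures how often one doctor's conclusion matches another's. It can be read as accuracy only if the second conclusion was reached without leaning on the first. Here one person may see the doctor's diagnosis, plan and assessed results, then form the reference diagnosis, then mark the doctor. An expert who has read a plausible diagnosis is more likely to settle on it.

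Blinding to DSS use does not prevent this, because the pull comes from the doctor's conclusion and not from knowledge of the arm. Two quantities are at stake: the absolute level of agreement, which matters because the first primary objective asks whether the DSS is accurate, and the difference between arms. A larger sample would not remove the bias from either.

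**Working it through.** **Step 1: what the text fixes.**

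| Question | What the article says | Where |
|---|---|---|
| Who sets the reference? | Overseeing expert | Overseeing experts |
| Who reviews the doctor's diagnosis and plan? | Overseeing expert | Schedule of intervention |
| Who reviews the doctor's tests and assessed results? | Overseeing expert | Part I |
| Who rates the doctor's decisions? | Overseeing expert | Overseeing experts |
| What is the expert blinded to? | DSS use | Overseeing experts; Blinding |
| Is the expert blinded to the doctor's diagnosis or plan? | Not stated anywhere | – |
| Must the expert record a conclusion first? | Not stated anywhere | – |

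The Part I sentence on investigations does not by itself show that the expert sees the doctor's diagnosis. The Schedule of intervention and the rating sentence supply that.

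**Step 2: equal anchoring.** The article gives no expected agreement rates and no formal sample size calculation, so there is no figure of its own to reproduce. All rates below are assumptions. Let p be the agreement that an independent expert would find, and a the fraction of true disagreements that the expert turns into agreement after seeing the doctor's conclusion. Then

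p′ = p + a(1 − p), and p₁′ − p₀′ = (1 − a)(p₁ − p₀).

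With p₀ = 0.50, p₁ = 0.70 and a = 0.2:

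- control: 0.50 + 0.2 × 0.50 = 0.60
- DSS: 0.70 + 0.2 × 0.30 = 0.76
- difference: 0.16 = 0.8 × 0.20

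A true 20-point difference becomes 18, 16, 14 or 10 points at a = 0.1, 0.2, 0.3 or 0.5.

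**Step 3: effect on power.** Inputs are 100 per arm (Sequence generation) and α = 0.05 (Statistical analysis), taken as two-sided. Agreement is treated as yes/no and clustering by doctor is ignored. With n = 100 and p̄ the mean of the two rates,

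z = [(p₁ − p₀) − 1.96 √(2p̄(1 − p̄)/n)] / √[(p₀(1 − p₀) + p₁(1 − p₁))/n].

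- 40 % v 60 %, a = 0: (0.200 − 0.1386)/0.0693 = 0.89, power 81 %.
- The same with a = 0.2, i.e. 52 % v 68 %: (0.160 − 0.1358)/0.0684 = 0.35, power 64 %.

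| True rates | a = 0 | a = 0.1 | a = 0.2 | a = 0.3 |
|---|---|---|---|---|
| 30 % v 50 % | 83 % | 73 % | 62 % | 52 % |
| 40 % v 60 % | 81 % | 73 % | 64 % | 55 % |
| 50 % v 70 % | 83 % | 76 % | 68 % | 60 % |

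**Step 4: unequal anchoring with no true effect.** With 40 % true agreement in both arms, a = 0.1 (control) and 0.2 (DSS) give 46 % v 52 %, a spurious 6 points and about a 13 % chance of a significant result favouring the DSS. With a = 0.1 and 0.3 the rates are 46 % v 58 %, 12 points and about 40 %. Nothing in the article shows that anchoring would differ between arms.

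**The case against.** The strongest reply is that Part I already describes an independent assessment. The patient goes to a separate clinic for a full diagnostic process, and the expert's plan is compared with the doctor's earlier one. Where the doctor's assessment "differs from the conclusion of the expert, the latter will decide on the final diagnosis and management plan of the patient", the wording implies that the expert has a conclusion of their own to compare. The order in which the form is completed may also be set out in the case report form or Additional file 2, neither of which is shown. Reading existing test results is ordinary clinical work. Table 3's fixed matching rules and the appeal to evidence-based guidelines limit discretion.

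Much of this stands. An expert-first reading is possible, so it cannot be said that the reference standard is dependent. But the article states positively that the same person reviews and rates, and elsewhere it describes the experts' task as verifying and certifying what the doctor decided. Matching rules do not help if the expert's own entry has been influenced.

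A reader might also infer that the arrangement favours the DSS: the experts belong to the consortium behind it, there are two per country for 50 patients, and DSS-guided work-ups might be recognisable. The article does not support that as a finding. Experts are blinded to DSS use, no recognisable pattern of tests or plans is described, both arms receive whatever investigations are required, and doctors may discard the DSS proposals. Arm recognition is a possibility only, and equal anchoring works against showing a benefit.

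**Conclusion.** The point holds in a limited form: independence of the reference standard is not secured by the text. The same expert sets the standard, reviews the doctor's conclusions and rates them, with blinding to DSS use only and no stated order of recording.

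The likelier consequence is inflated agreement in both arms and a diluted contrast, for example 16 points in place of 20 at a = 0.2. The size cannot be derived from the article, because both the agreement rates and a are assumed. This is a cheap improvement to the primary outcome of a feasibility study, held with medium confidence, and not a demonstrated failure of the design.

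**What to change.** State the order in the protocol and build it into the expert's case report form.

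1. The expert examines the patient with the raw test results, then records and signs the diagnosis or diagnoses and the plan.
2. Only then does the expert open the non-specialist's diagnosis, interpretation and plan, to settle care.
3. Table 3 is scored from the two signed entries, blind to arm, under equivalence and coding rules written in advance. The expert's own correct/incorrect rating is not used for the primary outcome. This also settles how a two-level rating relates to Table 3's graded scores.

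No extra assessor or visit is needed. The cost is a few more minutes per expert visit and the work of writing rules for when differently worded diagnoses or plans count as the same, which needs clinical input. The raw results still show which tests were ordered, so the change does not remove every possible clue to the arm.

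The Trial status section puts recruitment from March to September 2016. If it is under way, apply the order to the remaining patients and report which order was used for the earlier ones, since the two reference procedures would otherwise be mixed unseen.
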